### 2.2. Recruitment and Consent

Participants will be recruited from the community via public notice board flyers, word of mouth, or publicity generated by media outlets, e.g., newspaper articles, radio announcements, or social media networks/groups, detailing the PBDS. Potential participants are invited to contact study investigators via phone or in person to clarify details of the study. They will be provided with the participant information statement and consent form and must return the completed consent form, including signature and date, to the investigators as a mandatory requirement for enrolment in the study. Eligibility will be assessed by lead investigators by phone or in person using the study eligibility checklist. Individuals who participated in earlier studies at our research facility will also be invited to participate.

### 2.3. Study Regime

Data will be collected from consented enrolled participants once via two locations on the same day (or no more than 1–2 days apart) after an overnight fast (~10–12 h). First, body composition and bone density will be measured by a trained technician at the Newcastle Bone Density Centre (Waratah, NSW, Australia), and the remaining measurements and data will be collected at the Nutraceuticals Research Program at the University of Newcastle (Callaghan, NSW, Australia). These measurements will be conducted by the lead investigator and include seated blood pressure; waist circumference; diet history; medical, demographic, ethnicity, and physical activity history; and fasted blood samples for lipaemic parameters (total cholesterol, LDL-cholesterol, HDL-cholesterol, triglycerides, and total:HDL-cholesterol ratio), glycaemic parameters (glucose, insulin, and HbA1c), pro-inflammatory mediators (e.g., tumour necrosis factors alpha (TNF-α)), high-sensitivity C-reactive protein (hsCRP), full blood count, vitamin D, and liver function (Figure 1). Table 3 summarises data collected by participants unaided via self-administered questionnaires and data collected with assistance of a study investigator. All questionnaires have been either used in routine clinical care or were previously validated, and references are included within the tables, where appropriate. This cross-sectional study collects information from a singular time-point. Participants will be asked to provide consent to be contacted for potential future research.

The data will be stored on the University of Newcastle’s secure cloud-based system, which is suitable to host files that have large data or computing requirements. All electronic files will be password-protected as will be any study computers or laptops used for data entry in the first instance. The lead study investigator will enter the data, and double data entry and random cross-validation methods on the dataset will be routinely implemented to ensure validity, accuracy, and quality of the data.

### 2.4. Primary Outcomes

The primary outcome of this study is the 10-year and 5-year risk of developing CVD.

The Framingham Risk Equation (2008) [15] is a single multivariable risk function that will be used to calculate the 10-year risk of developing atherosclerotic CVDs defined as coronary death, myocardial infarction, coronary insufficiency, angina, ischaemic stroke, transient ischaemic attack, haemorrhagic stroke, peripheral artery disease, and heart failure. This equation was developed from the long-running Framingham Heart Study and is targeted at individuals aged 30 to 74 years of age without CVD at baseline examination [16]. There are two versions of the equation; the version which uses lipids will be used for this study. Variables that are required for the equation include (1) sex; (2) age; (3) total cholesterol; (4) HDL-cholesterol; (5) systolic blood pressure; (6) treatment status for hypertension; (7) smoking status; and (8) diabetes status. The Framingham Risk Equation has been validated in non-Indigenous Australian adults, with the 2008 equation reported to perform better than previous Framingham Risk equations at predicting cardiovascular outcomes in relatively young, healthy Australians. Therefore, the 2008 Framingham Risk Equation will be used for this study [17].

The 5-year absolute CVD risk will be estimated using the Australian Absolute CVD Risk Calculator [18] developed by the National Stroke Foundation on behalf of the National Vascular Disease Prevention Alliance (NVDPA), now part of the Australian Chronic Disease Prevention Alliance (ACDPA), with partner agencies and expert clinicians [19]. The Australian Absolute CVD Risk Calculator is also based on the Framingham Risk Equation. Descriptors of risk categories in the Australian context will be defined as in the Guidelines for the Assessment of Absolute Cardiovascular Disease Risk (2009) [19,20] and are presented in Table 4.

### 2.5. Secondary Outcomes

This study has the following secondary outcomes to investigate across various PBD and regular meat-eating diets: (1) dietary profile, such as dietary intake and food choices, across the five food groups; (2) diet quality and nutritional adequacy; (3) body composition and anthropometric measures; (4) bone mineral density; (5) biochemical parameters; and (6) medical, demographic, lifestyle, and physical activity characteristics. Secondary analyses of duration of following dietary pattern may be explored using a dose–response analysis, with the number of years being the exposure variable. Only sex would be adjusted for, as other variables are influenced by time.

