#### 2.6.4. Dietary Assessment

The Australian Eating Survey^®^ (AES) is a self-administered, validated, and reliable FFQ used to measure usual food and nutrient intake over the past 3 to 6 months [14]. The AES will be used to categorise dietary patterns, investigate the dietary profile of various dietary patterns, and assess diet quality and nutrient intake. The AES FFQ uses a subset of 70 questions related to core nutrient-dense foods recommended in the Australian Dietary Guidelines [23] and has been evaluated in Australian populations from the age of two years and is based on 15 years of research [14]. The Australian Recommended Food Score (ARFS) will be used to investigate diet quality across dietary patterns groups. The ARFS is derived from the AES FFQ by summing the points within eight sub-scales, as previously reported [24]. A comprehensive diet history capturing habitual food, beverage, and supplement intake for two typical days will also be collected during the appointment with the study coordinator who is also an Accredited Practising Dietitian and Accredited Nutritionist. An average of nutrient intake across the two days will be used to confirm findings from the FFQ, including directive questioning around motivations towards dietary patterns, such as *‘How long have you been consuming this type of dietary pattern?*’, ‘*What made you commence eating this type of dietary pattern?’,* and, when relevant, *‘What dietary pattern where you previously following?’* Other characteristics around dietary patterns will also be summarised, for example, frequency of consumption of dairy alternatives, plant-based meat alternatives, and their fortification status. Dietary pattern data from the AES and diet histories will be compared against the current 2013 Australian Dietary Guidelines (qualitatively) [23], and macronutrient and micronutrient data will be compared against the Nutrient Reference Values for Australia and New Zealand (quantitatively) [25]. Dietary intakes assessed from diet histories will be summarised and quantified using FoodWorks (Xyris^®^, Brisbane, Australia, sourced online).

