### 2.8. Statistical Analyses

All data will be assessed for normality by inspecting visual plots, such as histograms, quantile plots, and Q-Q plots, within each dietary pattern group for each variable. One-way ANOVA or Kruskal–Wallis tests will be used for comparison of CVD risk scores, dietary intake, and cardiometabolic parameters, including all clinical measures, medical/demographics, and blood parameters across dietary pattern groups. Chi-square or Fisher’s Exact tests will be used to compare qualitative dietary intake data and other categorical data across dietary pattern groups. Directed acyclic graphs (DAGs) will be used to display dependencies between outcome (5-year absolute CVD risk and 10-year CVD risk scores), exposure (different categories of dietary patterns determined via classifications presented in Table 1), and confounding/mediating variables to determine the minimum set of variables necessary to control for confounding [33] (Figure 2). Linear regression will be used to account for potential confounding factors described in the DAGs, such as age, sex, alcohol use, smoking status, and physical activity levels. Mediation analysis will be used to estimate the effect of PBDs on CVD risk that is not mediated through BMI [33,34]. Predictably, there will be intrinsic differences between dietary pattern groups, as the study design endeavours to evaluate the true characteristic of each group (chronic diseases, lifestyle choices, etc.). To address this and remove risk of overadjustment, a sensitivity analysis will be performed on potential additional important confounding variables not already identified in the DAGs to assess how robust the results are when comparting the additional confounding factor [35,36]. *p*-values will be adjusted using the Benjamini–Hochberg method to control the False Discovery Rate to 5%.

All statistical analyses will be conducted using StataCorp. 2015. *Stata Statistical Software: Release 14* (College Station, TX, USA: StataCorp LP). Continuous data will be presented as means, SD, median, and interquartile range (25th–75th percentile), and categorical data will be summarised as frequencies and percentages.

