**Figure 2 nutrients-15-02850-f002:**
[figure not shown]
Directed acyclic graph showing independence among potential confounding and mediating variables on the association between PBDs and CVD risk. Confounding factors are age, sex, alcohol use, smoking status, and physical activity levels, and BMI is a mediator. BMI, body mass index; PBDs, plant-based diets; CVD, cardiovascular disease.

**Table 2 nutrients-15-02850-t002:** Classification of dietary pattern groups by the number of time(s) foods are consumed, on average, per week.

	Vegan	Lacto-Ovo Vegetarian	Semi-Vegetarian	Pesco-Vegetarian	Regular Meat-Eater
Times per week consumed:					
Red meats:	0	0	≤1	0	0 or ≥1
Beef, kangaroo, veal, lamb, pork, etc.					
White meats:	0	0	≤1	0	0 or ≥1
Chicken, turkey, duck, etc.					
Processed/cured meats:	0	0	≤1	0	0 or ≥1
Bacon, corned beef, luncheon meats, such as ham, prosciutto, salami, etc., sausages, frankfurters					
*Seafood:* Fish (including tinned), crustaceans, oysters, squid, mussels, etc.	0	0	0 or ≤1	≥1	0 or ≥1
**Total of above categories**	0	0	≤2	≥1	≥7
Usual eating habits					
Animal-based dairy products (milk, cheese, ice-cream, butter, cream, margarine blends, etc.)	Nil	Y	N/A	N/A	N/A
Eggs	Nil	Y	N/A	N/A	N/A

Defining characteristics of dietary patterns are adapted from those previously implemented in Australian cohorts by Ferguson et al. [12] and Mihrshahi et al. [10]. ‘N/A’ denotes characteristics that were not relevant and, thus, not used for categorizing into respective diet groups.

**Table 3 nutrients-15-02850-t003:** Questionnaires, histories, measures, and biochemical samples completed by participants unaided and with assistance of a study investigator.

Item	Measures and Tools	Collected by Researcher or Participant ^1^
Medical history, medication/supplement use, and family medical history	Medical and Demographic Questionnaire	Participant
Demographics, ethnicity, socio-economic status, education history, employment history, smoking history, habitual alcohol intake, marital status, household food, and social history	Medical and Demographic Questionnaire	Participant
Physical activity	International Physical Activity Questionnaire (IPAQ-Long Form 2002) [13]	Participant
Dietary intake (qualitative), diet quality	Australian Eating Survey Food Frequency Questionnaire (AES FFQ) [14]	Participant
Food and nutrient intake (quantitative) and dietary pattern characteristics	Diet history via Accredited Practicing Dietitian	Researcher

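### The optional duration analysis is written with years and sex only; fitted across all five diets it mixes two kinds of year, and it leaves out age however the groups are handled

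*Protocol article*

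**What the plan says.** Section 2.5 opens by listing "secondary outcomes to investigate across various PBD and regular meat-eating diets", numbered (1) to (6). It then adds: "Secondary analyses of duration of following dietary pattern may be explored using a dose–response analysis, with the number of years being the exposure variable". The adjustment set follows: "Only sex would be adjusted for, as other variables are influenced by time".

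Duration is collected in the diet history (section 2.6.4) by asking "How long have you been consuming this type of dietary pattern" and, when relevant, "What dietary pattern where you previously following".

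Two other places bear on age. Section 2.4 says of the Framingham score: "Variables that are required for the equation include (1) sex; (2) age", followed by the remaining inputs. The caption of Figure 2 states: "Confounding factors are age, sex, alcohol use, smoking status, and physical activity levels, and BMI is a mediator".

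The diet contrast itself is assigned to section 2.8: ANOVA or Kruskal–Wallis tests across groups, and linear regression with diet category as the exposure and the Figure 2 confounders as covariates.

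**The concern.** The text fixes a model: one years variable plus sex. Two faults follow if it is fitted as written to everyone.

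- **The dose is not one quantity.** For a regular meat-eater, years on the pattern may be close to lifelong. For a plant-based eater it is years since adoption. If plant-based years lower the score and meat-eating years do not, a single slope averages unlike things and also absorbs the difference in level between the diets.
- **Age is left out.** Older people can have longer durations, and age directly raises the calculated score. The reason given for adjusting only for sex could apply to variables that change after a diet is adopted, such as BMI. It does not apply to age, which is not a consequence of diet duration.

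This is the only dose-response analysis the article describes. A null or positive slope could be read as showing that longer plant-based eating brings no benefit.

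**Working it through.** The article gives no figure for the duration analysis. Its one design figure reproduces: 2 × (1.96 + 0.84)² × 5.77² / 3.33² ≈ 47.1, rounded up to 48 per group, × 5 = 240. Four plant-based groups give 4 × 48 = 192.

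**Inputs from the article:** 48 per group; ages 35–75; a difference of 3.33 points. **Assumed, because the article does not give them:** age uniform (mean 55, variance 40²/12 = 133.3); plant-based duration exponential with mean 10 years (variance 100) and unrelated to age; meat-eaters' duration equal to age; log score rising 6% per year of age; true effect −1% per plant-based year and none per meat-eating year.

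**Pooled slope by hand** (meat-eaters are 0.2 of the sample):

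- Variance of years = 0.8 × 100 + 0.2 × 133.3 + 0.2 × 0.8 × (55 − 10)² = 80 + 26.7 + 324 = 430.7.
- Diet part of the covariance: within plant-based groups 0.8 × (−1) × 100 = −80; between diets 0.16 × 45 × 10 = +72; net −8. Contribution to the slope: −8 / 430.7 ≈ −0.02% per year.
- Age part: 6 × 0.2 × 133.3 = 160. Contribution: 160 / 430.7 ≈ +0.37% per year.
- Sex-only pooled slope ≈ −0.02 + 0.37 = +0.35% per year. With age in the model, only the near-zero diet part remains.

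The cancellation of −80 against +72 is the dose-definition fault. The +0.37% is the age fault.

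**Simulation on the same scale** (residual SD 0.35, true effect −1%):

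| Model | Mean slope per year |
|---|---|
| Pooled, sex only | +0.36% to +0.39% |
| Pooled, sex only, no true effect | about +0.37% |
| Pooled, sex and age | about 0.00% |
| Plant-based only, diet group and sex | −0.93% |
| Plant-based only, diet group, sex and age | −0.99% |

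Twelve settings were tried: mean plant-based duration 5, 10 or 15 years; meat-eaters' duration all of age or 50–100% of it; effect −1% or −2%. The sex-only pooled slope was positive on average in 11. The age-adjusted pooled slope ran from +0.12% to −0.56%, always short of the truth. The plant-based-only model with diet group and age recovered the truth in all 12.

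**When plant-based duration rises with age**, the sex-only pooled slope reaches about +1.0%. Restricting to the plant-based groups without age then gives +1.5% to +3.3% under a true −1%, depending on how strong the link is. Adding age restores −1.0%.

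**Separate check in score points** (residual SD 4, plant-based duration about 10 years and rising with age, meat-eaters' years close to age):

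- A diet gap of 3.33 with no duration or age effect: pooled slope +0.06 per year; 0.00 with a diet term.
- No diet or duration effect, age effect 0.3 points per year: +0.08 within the plant-based groups; 0.00 once age is added.
- True slopes −0.10 (plant-based) and +0.10 (meat), age effect 0.3: pooled with sex only +0.13; pooled with age +0.10; five groups with diet main effects and age −0.06; plant-based only with age −0.10. In a five-group fit, diet main effects alone are therefore not enough.

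**The case against.** The strongest reply is that pooling is inferred. The duration sentence does not say that the five groups are fitted together or that meat-eaters are included, and the phrase covering all the diets introduces the numbered outcomes rather than this sentence. A fit within each diet, adjusted for sex, agrees with the wording. How groups are handled is also a detail that a condensed article may leave to the full protocol or SAP. Much of this stands: a reader might infer that the article commits to a pooled model, and it does not. What remains is that the article states an adjustment set and closes it at sex. That excludes age on any reading, and it leaves no diet term if the groups are fitted together.

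Three further inferences go too far.

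- A reader might conclude that the study's diet comparison is compromised. It does not rest on this slope; section 2.8 tests it separately with age among the confounders.
- A reader might take the positive pooled slope as the work of the mixed dose. Most of it is age. The mixed dose accounts for the lost signal that remains once age is added.
- A reader might want the dose redefined as total years with little or no meat, since a long-term vegetarian who turned vegan last year may be recorded as one year. The quoted questions ask for the duration of the current pattern and the identity of the previous one. They do not show that the length of the earlier pattern is collected. Total low-meat years would also merge vegan and semi-vegetarian years, so years on the current pattern is a legitimate exposure.

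**Conclusion.** The point holds in limited form, at low severity. As written, the optional analysis has no diet term, no restriction to the plant-based groups and no age term. If all five groups are fitted together, a true −1% per plant-based year appears as roughly +0.4% to +1.0% with sex only and roughly zero with age added. If the fit is within diets, the mixed dose disappears but the age bias remains.

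The sizes depend on assumed durations, age slope and residual spread, and are illustrative. The direction of the age bias depends on older participants having longer durations. The loss of signal after age adjustment depends on meat-eaters' durations being much longer than those of plant-based eaters.

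**What to change.** In section 2.5, replace the sex-only sentence and state the analysis set. For example: the duration analysis will be run in the four plant-based groups, with years on the current pattern as the exposure and diet group, sex and age as covariates; regular meat-eaters are not included.

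If all five groups are kept, specify a diet-by-years interaction with age in the model. The meat-eaters' slope should then not be interpreted if their years are close to their age, because the two are hardly separable. Restricting the groups or adding diet terms without age is not a repair.

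Use the previous-pattern answer only in a sensitivity analysis, for example by flagging participants who moved from another plant-based pattern.

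The cost is one or two sentences and, under restriction, 240 − 192 = 48 fewer participants in an exploratory analysis. Age, sex, diet group and years on the current pattern are already part of the planned data, so no new collection is needed.

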## 2. Materials and Methods

### 2.1. Study Design and Setting

The PBDS is a cross-sectional study conducted at the Nutraceuticals Research Program, School of Biomedical Sciences & Pharmacy, University of Newcastle, Callaghan NSW, Australia. Eligible participants (Table 1) will be invited for one timepoint of data collection to examine the dietary profile, diet quality, nutritional status, and risk of developing CVD in adults consuming various PBDs and regular meat-eating diets (RMDs). To enhance representativeness of the Australian adult population and to gain a true understanding of the characteristics of the dietary patterns of interest, every effort will be made to invite all eligible individuals to participate in the study, including those with chronic health conditions.

**Table 1 nutrients-15-02850-t001:** Inclusion and exclusion criteria for the PBDS.

Inclusion Criteria	Exclusion Criteria
Adults ages 35–75 years.	Ages <35 and >75 years.
No history of CVD, such as myocardial infarction, coronary insufficiency, angina, ischaemic stroke, transient ischaemic attack, haemorrhagic stroke, peripheral artery disease, heart failure, or pacemaker implant.	Receiving treatment for CVDs.
Consuming one of the following dietary patterns in Table 2 for at least 6 months; (1) vegan, (2) lacto-ovo vegetarian, (3) semi-vegetarian, (4) pesco-vegetarian, and (5) regular meat-eaters.	Made significant changes to their dietary pattern, food choices, lifestyle and/or physical activity levels in the past 6 months (determined by an Accredited Practising Dietitian) and/or practicing in (or in the last 30 days) another research trial involving dietary and/or physical activity intervention.
	Pregnant/lactating.

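### The optional analysis by years on the diet adjusts for sex only, for a reason that does not apply to age, so its slope may mix ageing with duration

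*Protocol article*

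**What the plan says.** Section 2.5 introduces the analysis as a possibility: "Secondary analyses of duration of following dietary pattern may be explored using a dose–response analysis, with the number of years being the exposure variable". It then fixes the adjustment set and gives a reason: "Only sex would be adjusted for, as other variables are influenced by time". It names no outcome for this analysis and does not say whether regular meat-eaters are included.

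Four other places bear on the choice:

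- Section 2.4 makes age a component of the 10-year score: "Variables that are required for the equation include (1) sex; (2) age; (3) total cholesterol; (4) HDL-cholesterol; (5) systolic blood pressure". The 5-year score has the same basis: "The Australian Absolute CVD Risk Calculator is also based on the Framingham Risk Equation".
- Section 2.8 adjusts the main diet-category analysis for age: "Linear regression will be used to account for potential confounding factors described in the DAGs, such as age, sex, alcohol use, smoking status".
- The Figure 2 legend classifies the variables for that same analysis: "Confounding factors are age, sex, alcohol use, smoking status, and physical activity levels, and BMI is a mediator".
- Table 1 admits a wide age span ("Adults ages 35–75 years") and requires at least six months on the diet, with no upper limit.

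Nothing elsewhere in the article brings age back into the duration analysis or handles it another way.

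**The concern.** The exclusion of age is a stated rule with a stated reason, not a detail left for a later analysis plan. The reason can be defended for variables that might change because of the diet, BMI being the clearest. It cannot be defended for age. Age passes with time whatever a person eats, it caps the number of years anyone can have followed a diet, and it enters the risk score directly. When the exposure is itself elapsed time, a variable with those properties is a confounder, not a consequence of exposure.

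Without age in the model, the duration slope may carry part of the age gradient in the score. That gradient is positive, so the bias runs one way: longer adherence may look harmful, or a true benefit may be masked or reversed. Section 2.10.4 says that findings are meant to inform policy and dietary guidelines, so a misleading slope on this question would matter.

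**Working it through.** **Figure that the plan gives.** There is none for the duration analysis. The group size used below comes from Section 2.7 (difference 3.33, SD 5.77, 80% power, 0.05 taken as two-sided):

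n per group = 2 × (1.960 + 0.842)² × 5.77² / 3.33² ≈ 47.1, rounded up to 48.

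This reproduces the stated 48 per group and 5 × 48 = 240. The four plant-based groups hold 4 × 48 = 192.

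**Assumed inputs.** The document gives neither the correlation of age with the score nor that of age with duration. I take 0.5 to 0.7 for the first and let the second run from 0 to 0.5. The outcome is assumed to be the CVD risk score.

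**Formula.** If duration has no effect once age is known, the correlation that appears when age is left out is

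r(spurious) = r(age, duration) × r(age, score).

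The chance that a two-sided 5% test rejects, using Fisher's z with one covariate (sex) in the model, is

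Φ(√(n − 4) × atanh(r) − 1.96) + Φ(−√(n − 4) × atanh(r) − 1.96).

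Example: r = 0.2 × 0.5 = 0.10 and n = 192. √188 × atanh(0.10) = 13.71 × 0.1003 = 1.376, and 1.376 − 1.96 = −0.584, so the chance is 0.28. The spurious slope per SD of duration is r × 5.77.

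| r(age, duration) | Spurious r | False-positive rate | Spurious slope, score points per SD of duration |
|---|---|---|---|
| 0 | 0 | 5% | 0 |
| 0.1 | 0.05–0.07 | 10–16% | 0.29–0.40 |
| 0.2 | 0.10–0.14 | 28–49% | 0.58–0.81 |
| 0.3 | 0.15–0.21 | 54–83% | 0.87–1.21 |
| 0.4 | 0.20–0.28 | 79–98% | 1.15–1.62 |
| 0.5 | 0.25–0.35 | 94% to above 99% | 1.44–2.02 |

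**What correlations could arise.** The simulation drew age uniformly over 35–75, used an SD of 5.77, no true duration effect, n = 192 and the same range for r(age, score). Sex was left out for simplicity.

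| Assumed adoption pattern | r(age, duration) | Spurious slope per 10 years | Rejection without age |
|---|---|---|---|
| Start uniform from age 15 to half a year before the visit | 0.44 | 0.96–1.34 | 87–99% |
| Half on the diet since age 18, the rest 0.5–10 years | 0.32 | 0.52–0.73 | 62–90% |
| Log-uniform durations, from 0.5 years | 0.19 | 0.53–0.73 | 26–43% |
| Mostly recent, nearly unrelated to age (0.5 years plus exponential, mean 8 years) | 0.02 | 0.07–0.09 | 5–6% |

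Adding age to the model brought rejection to 4.7–5.5% in every scenario.

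**The case against.** Several objections carry weight.

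- **The analysis is optional and secondary.** The primary comparison, the sample size and the age-adjusted main regression do not depend on it. This stands and limits the severity.
- **No outcome is named.** The point that age is built into the score, and the assumed age-score correlations, apply only if the outcome is the CVD risk score. This stands. Age could plausibly confound other outcomes, such as bone density, but the figures above do not carry over to them.
- **Adoption may be mostly recent.** The Introduction describes a rapid recent rise in uptake, and Table 1 asks for only six months. If duration is almost unrelated to age, the inflation is negligible. This stands as a live possibility, though recent adoption does not by itself make duration independent of age.
- **Multiplicity.** Section 2.8 applies Benjamini–Hochberg. If that covers this analysis, rejection rates would be no higher than shown and usually lower. It would not change the biased slope.
- **The DAG.** A reader might infer that Figure 2 directly contradicts Section 2.5. It does not: it models diet category, not duration. It shows that the protocol treats age as a confounder in the main analysis, which makes the omission here inconsistent in reasoning, not a literal contradiction.
- **Other covariates.** A reader might also want alcohol, smoking and physical activity restored. These may change after a diet is adopted, so the protocol's caution is arguable for them.

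None of this rescues the stated reason as applied to age.

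**Conclusion.** The sentence is wrong as written and should be fixed. Its reason does not cover age, and the article treats age as a confounder elsewhere.

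The size of the harm is open. With no true effect, n = 192 and an assumed age-score correlation of 0.5 to 0.7, the unadjusted false-positive rate runs from about 5% to 94% or more as the age-duration correlation goes from near 0 to 0.5. This rests on the CVD risk score being the outcome and on correlations that the document does not supply.

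A reader might go further and conclude that the analysis will mainly show that older people have higher scores, or that the study's main result is at risk. The document supports neither. The first depends on an unknown correlation that could be small, and the second does not follow from an optional secondary analysis. What can be said is that a significant slope from the model as planned could not be attributed to duration.

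**What to change.** Replace the adjustment sentence in Section 2.5 with wording such as:

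> The analysis will be adjusted for age and sex, with age allowed to be non-linear; variables that may be consequences of the diet, such as BMI, are not adjusted for.

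Name the outcome. Fit the model in the plant-based groups with diet group as a covariate. Include regular meat-eaters only if their duration can be distinguished from age, since for someone who has always eaten meat the two nearly coincide. Do not add age at adoption as a third term: it equals age minus duration, so only two of the three can enter one model.

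The cost is one sentence and no new data, because age is already collected. Some precision is lost because age and duration are correlated. For the same residual variance, the variance of the duration slope is multiplied by 1/(1 − r²): 1/(1 − 0.04) = 1.04 at r = 0.2 and 1/(1 − 0.25) = 1.33 at r = 0.5.
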